### Data-analysis

Primary effects will be calculated using multilevel regression analysis, for somatic and DSC units separately. The GDS-8-scores and CSDD-scores will be used in the primary analysis. Age, sex, cultural background and cognitive status will be used as covariates. The EQ5D will be analyzed as another primary outcome in the intervention study. For cost analysis, see economic evaluation. A process analysis will be carried out to determine the actual use of the components of the psychosocial, psychological and pharmacological treatment, and to determine facilitators and obstacles.

Secondary outcomes (percentage accuracy of depression-detection in usual care, prevalence of depression-diagnosis in the intervention group and response to treatment of depressed residents) will be analyzed using descriptive statistics.

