**Methods/Design:**

In a 19-month longitudinal controlled study using a stepped wedge design, 14 somatic and 14 dementia special care units will implement the care program. All residents who give informed consent on the participating units will be included. Primary outcomes are the frequency of depression on the units and quality of life of residents on the units. The effect of the care program will be estimated using multilevel regression analysis. Secondary outcomes include accuracy of depression-detection in usual care, prevalence of depression-diagnosis in the intervention group, and response to treatment of depressed residents. An economic evaluation from a health care perspective will also be carried out.

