### Measurements

*Primary outcomes *are frequency of depression and quality of life.

Frequency of depression (the percentage of residents with depression on a unit) is measured in somatic residents by a shortened version of the Geriatric Depression Scale (GDS)[43], the 8-item GDS-nursing home version (GDS-8) of Jongenelis et al. [28], which was made by deleting GDS-items that are not applicable to most NH residents. The GDS-8 was validated in the AGED dataset, where it showed a good internal consistency of α = .80 and high sensitivity rates of 96.3% for major depression and 83.0% for minor depression, with a specificity rate of 71.7% at a cut-off score of 3 or more [28]. The GDS-8 also appears to be able to assess (change in) severity of depression [44]. The GDS-30 is originally a self-report instrument, the GDS-8 is interview based.

Frequency of depression in dementia residents is measured by the Cornell Scale for Depression in Dementia (CSDD)[29]. The CSDD is administered through interviewing nursing staff about their observations of the residents' behavior. The CSDD consists of 19 items each rated as 0 = absent, 1 = mild or intermittent and 2 = severe. The scores of the individual items are summed and a cut-off of 8 or more indicates depression [29]. Vida et al. [30] reported for a cut-off score of 8 or more, a sensitivity of 90% and specificity of 75% in residents with Alzheimer's Disease.

Quality of life in somatic residents is measured by the EQ-5D [45]. The EQ-5D instrument is a standardized non disease-specific instrument for describing and valuing Health Related Quality of Life [46]. There are two core components of the instrument: a description of the respondent's 'own health' using a health state classification system with five domains (mobility, self-care, usual activities, pain/discomfort and anxiety/depression) and a rating of 'own general health' by means of a visual analogue 'thermometer' scale. The EQ5D has shown a good validity and good test-retest reliability [47,48].

In dementia residents quality of life is measured by the EQ-5D proxy version [49]. Thereto, nursing staff are asked to score the scale for the resident.

Secondary outcomes are percentage accuracy of depression-detection in usual care, prevalence of depression-diagnosis in the intervention group, and response to treatment of depressed residents.

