### Economic evaluation

This study investigates the efficiency of the care program AID compared to usual care as provided in NH units. If the program AID turns out to be successful, a decrease in the prevalence of depression in NH will occur. On the one hand the program needs investment in for example training of nursing staff and, consequently, generates extra costs compared to usual care. On the other hand it potentially generates savings as it reduces depression related time investment in NH.

The economic evaluation is based on the general principles of a cost-effectiveness analysis from a healthcare viewpoint. Based on the above mentioned primary outcomes, two different incremental cost effectiveness ratios (ICERs) will be computed, answering the questions: 'How much money has to be invested additionally in the care program to gain one percentage point decrease in frequency of depression?' and 'How much money has to be invested additionally in the care program to gain one Quality-Adjusted Life Year (QALY)?'

The cost analysis consists of two main parts. First, on resident level, volumes of care (to determine the incremental direct health care costs) based on the production process of the care program and of depression decrease are measured prospectively using an activity based costing approach. Focusing on activities performed with costs accumulated at the activity level(s) of the health care production processes, standardized case report forms are used to assess time invested by nursing staff, psychologist, elderly care physician and recreational therapist. Also, number of hospital admissions (number of days in hospital) and use of antidepressant medication are recorded.

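### The primary depression outcome is a percentage of residents above a cut-off, but the analysis section names the GDS-8 and CSDD scores and no cut-off, so the scale of the primary result is not fixed

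*Protocol article*

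**What the plan says.** Four parts of the protocol article describe the depression outcome as a proportion.

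- **Abstract, Methods/Design:** "Primary outcomes are the frequency of depression on the units and quality of life of residents on the units".
- **Measurements:** the primary outcomes "are frequency of depression and quality of life", and the first is spelled out: "Frequency of depression (the percentage of residents with depression on a unit) is measured in somatic residents" by the GDS-8, with the CSDD used in dementia residents. The cut-offs are in the same section. For the CSDD, "a cut-off of 8 or more indicates depression". For the GDS-8, the cut-off appears as part of the validation result, "with a specificity rate of 71.7% at a cut-off score of 3 or more".
- **Sampling:** the inputs are depression prevalence (22% somatic, 30% dementia special care, DSC) and remission rate (40% and 35%). No mean score, score difference or standard deviation is given.
- **Economic evaluation:** the first cost-effectiveness ratio asks what must be spent "to gain one percentage point decrease in frequency of depression".

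The Data-analysis section specifies multilevel regression, run separately for the two unit types, and then says: "The GDS-8-scores and CSDD-scores will be used in the primary analysis". This is the only sentence that names the variable to be analysed for depression. It mentions no cut-off, proportion or type of regression model.

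**The concern.** A difference in mean score and a difference in the proportion above a cut-off are different effects, and they can disagree. Taken at its word, the Data-analysis section tests the first while the outcome definition, the sample size and the cost-effectiveness ratio all concern the second. The primary p-value would then not refer to the stated primary outcome.

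If the sentence is instead shorthand for scores split at the cut-offs, it leaves that unsaid. Measurements also remarks that the GDS-8 can capture change in severity, so a score analysis would look just as defensible as a frequency analysis. With two plausible versions of the primary result and none fixed, the scale can be picked once the results are known.

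**Working it through.** **1. Does the planned sample size belong to a proportion?**

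Inputs from Sampling: 14 units per type, 6 measurements, alpha 0.05, power 0.80, ICC 0.1; somatic 25 residents per unit with 20% attrition; DSC 20 residents per unit with negligible attrition. From Methods/Design: 5 groups crossing over in turn.

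Assumptions, because the article does not state them: two-sided alpha; attrition leaves 25 × 0.80 = 20 residents per somatic unit; remission acts as a relative fall in prevalence; the 14 units split 3, 3, 3, 3, 2 over the groups. This gives:

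- somatic: 22% × (1 − 0.40) = 13.2%, difference 8.8 points
- DSC: 30% × (1 − 0.35) = 19.5%, difference 10.5 points

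Hussey-Hughes variance of the effect, with I = 14 units, T = 6 periods, m = 20 residents, v = mean of p(1 − p), s² = 0.9v/m and t² = 0.1v:

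Var = I·s²(s² + T·t²) / [(I·U − W)s² + (U² + I·T·U − T·W − I·V)t²]

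For this layout:

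- U = 44, W = 466, V = 164
- I·U − W = 616 − 466 = 150
- U² + I·T·U − T·W − I·V = 1936 + 3696 − 2796 − 2296 = 540

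Somatic:

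- v = (0.1716 + 0.1146)/2 = 0.1431, s² = 0.00644, t² = 0.01431
- Var = 0.00832/8.693 = 0.000957, SE = 0.0309
- power = Φ(0.088/0.0309 − 1.96) = 0.812; with 13 units it is 0.782

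DSC:

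- v = (0.2100 + 0.1570)/2 = 0.1835, SE = 0.0350
- power = Φ(0.105/0.0350 − 1.96) = 0.850; with 13 units it is 0.822

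Cross-check with the Woertman design effect for 20 residents per unit:

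- (12.9/7.9) × 2.7/9.6 = 0.459
- somatic: 2 × 293 × 0.459 = 269 residents, 269/20 = 13.46, rounded up to 14 units
- DSC: 2 × 264 × 0.459 = 242 residents, 242/20 = 12.1, rounded up to 13 units

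The larger requirement is 14, the planned figure. Other variance conventions, 25 instead of 20 residents per somatic unit, and other splits of the units move two-sided power at 14 units between 0.69 and 0.89 (somatic) and between 0.76 and 0.86 (DSC). The reproduction therefore depends on the assumptions, but every input to it is a proportion.

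**2. What would a score analysis mean for power?**

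The article gives nothing from which to size one. In standardised units, the same layout with 20 residents per unit detects (1.96 + 0.84) × SE = 0.23 SD at 80% power (0.21 SD with 25). If the score were normal and the prevalence falls came from a shift of the whole distribution, the shifts would be:

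- somatic: z(0.868) − z(0.780) = 0.345 SD
- DSC: z(0.805) − z(0.700) = 0.335 SD

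Power on the score would be about 0.98 or higher. This is an illustration under an assumed distribution, but it shows the direction.

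**3. Can the two effects disagree?**

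Take a DSC unit of 20 residents and the CSDD (19 items scored 0 to 2, cut-off 8), using invented residents:

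- One resident falls from 19 (every item scored 1) to 8. The unit mean drops by 11/20 = 0.55 and the frequency by 0.
- One resident falls from 8 to 7. The unit mean drops by 1/20 = 0.05 and the frequency by 1/20 = 5 percentage points.

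The larger score change gives no change in the stated outcome.

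**The case against.** The best defence is that the sentence names the data source and not the scale. Measurements says that frequency is measured with these two instruments, and the Economic evaluation repeats it. The next outcome in Data-analysis, the EQ-5D, is introduced as a further primary outcome, which implies that the preceding sentence is about frequency. Multilevel regression covers logistic models, and the article is a condensed document that may leave coding and link function to an analysis plan.

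Much of this stands. The article does not say that mean or continuous scores will be compared, so it cannot be asserted that the plan abandons the proportion. But it does not say the scores will be dichotomised either. Measurements itself separates the summed item scores from the cut-off that indicates depression. The point is therefore not a detail left out: the one statement about the analysed variable does not match the outcome definition, and an analysis plan faithful to one section would depart from the other.

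A reader might infer three stronger things, none of which the document supports.

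- **That the trial is underpowered for its analysis.** The stated power was not calculated for a score, but a score analysis would usually have more power.
- **That the false-positive risk rises to 1 − 0.95² = 9.75% per unit type.** This requires testing both versions as primary, which no section plans, and treating them as independent, although one is a function of the other.
- **That the first cost-effectiveness ratio cannot be obtained.** The economic evaluation names frequency as its own effect measure, and a percentage-point difference can be computed from the same data. The fair criticism is only that it might not agree with the primary analysis.

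**Conclusion.** The mismatch holds. Outcome definition, sample size and first cost-effectiveness ratio all refer to a proportion, while the analysis sentence refers to scores and gives no cut-off. Either the primary test estimates something other than the stated outcome, or the scale of the primary result has not been fixed in advance.

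The damage is to what the primary result means and to its pre-specification. It does not lie in lost power and has no error-rate figure attached. That the sample size was built on proportions is clear from its inputs alone. The agreement with 14 units rests further on reading remission as a relative fall in prevalence (22% to 13.2%, 30% to 19.5%), on two-sided testing and on 20 analysable residents per unit, none of which the article states outright.

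**What to change.** Reword the Data-analysis section so that the dependent variable of the primary depression analysis is each resident's depression status at each measurement: GDS-8 of 3 or more in somatic units, CSDD of 8 or more in DSC units. Analyse it in a multilevel logistic model, separately by unit type as already planned. Report the effect also as a percentage-point difference, so that it is consistent with the first cost-effectiveness ratio. List the continuous GDS-8 and CSDD scores as a named supportive analysis. It would also help to state the GDS-8 cut-off in Measurements as the outcome definition, since it appears there only as a validation property.

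This is a change of wording. It needs no new data and keeps 14 units per type. The small downside is that a binary outcome uses the data less efficiently than the score, which is why the score analysis is worth keeping.

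Redefining the primary outcome as the score would also remove the mismatch. It costs more: the sample size would need a score difference and standard deviation that the article does not give, and the outcome definition and cost-effectiveness question would have to be revisited.

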## Methods/Design

The study is a stepped wedge, multicentre intervention study on 14 somatic and 14 Dementia Special Care (DSC) units of UKON-NH.

A stepped wedge design is a type of crossover design in which different clusters (here: units) cross over from the control group to the intervention group at different time points. All clusters are measured at each time point. The first time point corresponds to a baseline measurement where none of the clusters receive the intervention of interest; at the last time point all clusters receive the intervention. After intermediate time points, clusters initiate the intervention. More than one cluster may start the intervention at a time point, but the time a cluster begins the intervention is randomized [25] (see Figure 1 for a graphical representation of the design). This way, comparisons within units ánd between units will be available, making the design very powerful. Another advantage of the design is that all involved units will receive the intervention - which is expected to increase motivation for participating in the study.

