**Figure 1 F1:**
[figure not shown]
**Graphical representation of the stepped wedge design**. '0' represents measurement of usual care; control condition '1' represents measurement after the intervention has been implemented; intervention-condition

At the start of the data collection, the residents with informed consent of all 28 units are screened for depression (T0). Following this, each of the units is randomly assigned to one of 5 groups. Each group starts the intervention at different time points, directly after one of the measurements (T0-T4), which are each 4 months apart. In the four- month interval between T0 and T1, nursing staff of the first group is trained within the first month. After this month, the intervention runs for the subsequent 3 months in the first group before the second measurement (T1) of all 28 units takes place. After T1, the second group is trained, and the intervention starts in this group while it is continued in the first group. This procedure is repeated for the remaining 3 groups until, at the last measurement (T5), all 28 units are in the intervention condition. Consequently, the follow up in the intervention condition varies from 3 months for the last group, which starts with the intervention 1 month after T4, to 19 months for the first group, which starts after T0.

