### Sampling

We calculated the sample-size using the following assumptions.

For somatic units: 25 residents per unit [37], a depression prevalence of 22% [38], a remission rate of 40% [39], and an attrition of 20% [38].

For DSC units: 20 residents per unit [40], a depression prevalence of 30% [10,40-42], a remission rate of 35% [13], and negligible attrition [40].

Based on these assumptions and a significance level alpha of 0.05, a power of 0.80 and an ICC of 0.1 for both somatic and dementia residents, 14 clusters (units) with 6 measurements are needed in a stepped wedge design to allow multilevel analysis.

Given that the outcomes will be presented on unit-level, during the data collection, newly admitted residents and/or their legal representatives are asked to provide informed consent on all units. This way, the sample size is not influenced by death or relocation of participating residents and can remain stable.

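### The stated covariates of the primary model do not include measurement wave, so in this one-way stepped wedge a linear secular trend would load largely onto the programme effect

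*Protocol article*

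**What the plan says.** All of this is in the protocol article.

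- **Data-analysis, model:** "Primary effects will be calculated using multilevel regression analysis, for somatic and DSC units separately". The GDS-8, CSDD and EQ-5D are the outcomes.
- **Data-analysis, adjustment:** "Age, sex, cultural background and cognitive status will be used as covariates". Neither this section nor any other adds calendar time, period or wave.
- **Methods/Design, text with Figure 1:** "Each group starts the intervention at different time points, directly after one of the measurements (T0-T4), which are each 4 months apart". There are five groups and six measurements, and "at the last measurement (T5), all 28 units are in the intervention condition".
- **Sampling:** "14 clusters (units) with 6 measurements are needed in a stepped wedge design to allow multilevel analysis", with "a significance level alpha of 0.05, a power of 0.80 and an ICC of 0.1".
- **Economic evaluation:** the EQ-5D change compares mean values under control with mean values after 3 to 19 months of the programme. It says that the effect analysis follows the study design but names no time adjustment.

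**The concern.** In a parallel-group trial, randomisation balances calendar time between arms. In a stepped wedge it cannot, because within each unit all control measurements come before all intervention measurements. Randomising the start time makes the time effect separable from the programme effect, but only if the model contains a time term.

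The four listed covariates are resident characteristics. Age and cognitive status may absorb part of a change in case mix. They do not stand in for season, staffing or policy changes over the study. If depression fell for such reasons, an ineffective programme could look effective. If it rose, a real benefit could be hidden. Both primary outcomes and both cost-effectiveness ratios would be exposed.

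**Working it through.** **Inputs.** From Sampling: 14 units per stratum, 6 measurements, ICC 0.1, alpha 0.05 (taken as two-sided). Somatic: "For somatic units: 25 residents per unit [37], a depression prevalence of 22% [38], a remission rate of 40% [39], and an attrition of 20%". DSC: 20 residents per unit, prevalence 30%, remission 35%, negligible attrition. The planned effects are 22% × 0.40 = 8.8 points (to 13.2%) and 30% × 0.35 = 10.5 points (to 19.5%). Assumed here: units split 3/3/3/3/2 over the five groups, cross-sectional measurements and a random unit intercept.

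**Step 1. Timing.** Group g (g = 1 to 5) has control waves 0 to g−1, with mean (g−1)/2, and intervention waves g to 5, with mean (g+5)/2. The difference is 3 waves, or 12 months, in every group.

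**Step 2. Model.** Unit means over the six waves have covariance V = τ²J + (σ²/n)I, with τ² = 0.1·p(1−p) and σ² = 0.9·p(1−p). The standard error (SE) of the programme effect is the square root of its diagonal element in (Σ D′V⁻¹D)⁻¹. D holds the intervention indicator and either one intercept or six wave effects. Power = Φ(effect/SE − 1.96).

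**Step 3. The plan's own figure.** Power with 14 units:

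| Stratum, n per unit, p used for variance | With wave | Without wave |
|---|---|---|
| Somatic, 25, baseline 22% | 82.4% | 99.6% |
| Somatic, 25, midpoint 17.6% | 88.2% | 99.9% |
| Somatic, 20 (after attrition), baseline | 73.8% | 98.5% |
| Somatic, 20, midpoint | 80.7% | 99.4% |
| DSC, 20, baseline 30% | 80.0% | 99.4% |
| DSC, 20, midpoint 24.75% | 84.5% | 99.7% |

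With wave effects, 14 is the smallest number of units reaching 80% for somatic with n = 25 and for DSC with n = 20, both at baseline variance. It is also the smallest for somatic with n = 20 at midpoint variance. Without wave effects, 5 to 7 units would be enough. If p(1−p) is instead read as the within-unit variance, power with wave is 69% to 85%, and without wave it is still at least 97%.

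**Step 4. Loading of a linear trend.** The trend is entered in years (wave index × 4/12) with no programme effect. The expected programme coefficient without wave effects is 0.982 × the yearly drift (n = 20). T0 to T5 spans 20/12 = 1.667 years, so 0.982/1.667 = 59% of the total change is attributed to the programme. With wave effects the loading is 0.

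**Step 5. Rejection rate under no effect.** With bias b = 0.982 × drift, the rate is Φ(−1.96 − b/SE) + 1 − Φ(1.96 − b/SE). SE without wave (n = 20, midpoint variance) is 1.96 points for somatic and 2.22 for DSC. The drift sizes are assumptions.

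| Drift per year | Bias | Somatic: b/SE, rejection | DSC: b/SE, rejection |
|---|---|---|---|
| 2 points | 1.96 points | 1.00, 17% | 0.88, 14% |
| 3 points | 2.95 points | 1.50, 32% | 1.33, 26% |
| 4 points | 3.93 points | 2.00, 52% | 1.77, 42% |

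With wave effects the rate is 5% in each case. The SE is then 3.11 points (somatic) and 3.53 points (DSC).

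**The case against.** The strongest reply is that a short paragraph in a journal article is being read as a complete model. The sentence lists four resident characteristics and does not say that they are the only terms. The intervention indicator is not named either, and without it no programme effect could be estimated. A period term is as structural to a stepped wedge as that indicator, and both could stand in a fuller document. The sample size supports this reply, since 14 units match a wave-adjusted calculation.

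Most of that stands as regards intent. A reader might infer that the planners decided against time adjustment, or that sample size and analysis flatly contradict each other. The document supports neither. An unstated term explains the text as well as a contradiction does.

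It does not remove the point. The article names its adjustment set and leaves out the one adjustment that this design depends on. A reader who fits what is written gets a confounded estimate. The reference to following the design, in the economic evaluation, does not name a time term.

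Some limits also stand. The rejection rates rest on assumed drifts, because the document reports no trend. They are computed on prevalence, whereas the Data-analysis section refers to GDS-8 and CSDD scores, and none is computed for the EQ-5D.

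**Conclusion.** The concern holds for the model as described. With only the listed covariates, about 0.98 years of a linear secular trend, or 59% of the T0-T5 change, enters the programme effect. For assumed drifts of 2 to 4 points per year the nominal 5% test rejects in 17% to 52% (somatic) and 14% to 42% (DSC) of trials with no effect. These figures rest on a linear trend common to all units, the stated ICC of 0.1, 20 residents per measurement and a random unit intercept.

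Three stronger readings are not supported. Not every drift biases the estimate: a pattern unrelated to exposure would not. The smaller SE without wave (2.0 against 3.1 points, somatic) is a difference between two models, and it would be correct if there were no period effects. The match to 14 units depends on convention: wave-adjusted power runs from about 74% to 88% in the main table. What is robust is the gap to the unadjusted model, at 98.5% or more in the same table. The analysis text should be brought into line with the model that the sample size implies.

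**What to change.** State in the Data-analysis section that every primary model (GDS-8, CSDD, EQ-5D) contains measurement wave T0-T5 as a categorical fixed effect beside the intervention indicator, with random effects for unit and for repeated measures within resident. Keep age, sex, cultural background and cognitive status as further covariates. State in the Economic evaluation section that the effect estimates for depression frequency and utilities carry the same time adjustment.

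The cost is a sentence in each section and a larger SE than the unadjusted model would give. Power stays near the stated 80%, but under some variance conventions for somatic units it falls somewhat below (73.8% with 20 residents and baseline variance). The calculation above has no resident-level random effect, so it does not show what that term does to power.
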